## Abstract

**Background:**

To investigate the effect of physician- and patient-specific feedback with benchmarking on the quality of care in adults with type 2 diabetes mellitus (T2DM).

**Methods:**

Study centres in six European countries were randomised to either a benchmarking or control group. Physicians in both groups received feedback on modifiable outcome indicators (glycated haemoglobin [HbA_1c_], glycaemia, total cholesterol, high density lipoprotein-cholesterol, low density lipoprotein [LDL]-cholesterol and triglycerides) for each patient at 0, 4, 8 and 12 months, based on the four times yearly control visits recommended by international guidelines. The benchmarking group also received comparative results on three critical quality indicators of vascular risk (HbA_1c_, LDL-cholesterol and systolic blood pressure [SBP]), checked against the results of their colleagues from the same country, and versus pre-set targets. After 12 months of follow up, the percentage of patients achieving the pre-determined targets for the three critical quality indicators will be assessed in the two groups.

**Results:**

Recruitment was completed in December 2008 with 3994 evaluable patients.

**Conclusions:**

This paper discusses the study rationale and design of OPTIMISE, a randomised controlled study, that will help assess whether benchmarking is a useful clinical tool for improving outcomes in T2DM in primary care.

**Trial registration:**

NCT00681850

## Background

Physicians in Europe and throughout the world are diagnosing and treating a growing number of patients with type 2 diabetes mellitus (T2DM). The International Diabetes Federation estimates that approximately 55 million people in Europe had diabetes in 2010 [1]. Over 90% of these are patients with T2DM, and management of its associated complications already requires a significant level of support in terms of financial costs and healthcare utilisation [2]. In 2009 the healthcare expenditure for diabetes was estimated to account for 10% of the total health budget in Europe [1] and this financial burden, together with the accompanying social burden associated with reduced quality of life and productivity caused by the condition, its numerous comorbidities and premature death, is undoubtedly set to rise over the next decade.

Clinical research has shown that long-term complications of diabetes can be delayed or even prevented when management by the healthcare team and the patient's self-management are optimised [3-5]. However, the apparent inability to effectively translate this scientific evidence into real-life clinical practice represents a major barrier to reducing the burden of diabetes complications [6,7].

Western healthcare systems are currently in a transition phase; shifting towards organisational structures that can deliver improved diabetes care specifically, and chronic care in general [8,9]. T2DM is often used as 'the' test case for new models of care. The assumption is that if an intervention works in as complex a disease as T2DM, there is a fair likelihood that it will be effective in other chronic conditions. Because the majority of chronic illness care is performed within the primary care setting, redesign of primary care has been proposed in an attempt to close the gap between current practices and optimal standards [10]. How such a redesign might be accomplished is the subject of ongoing research and socio-economic debate, and in this process the Chronic Care Model is often used as a conceptual framework [11-13]. This model identifies six essential elements that impact upon chronic care: (i) community resources and policies, (ii) healthcare organisation, (iii) self-management support, (iv) delivery system design, (v) decision support, and (vi) clinical information systems [12]. Initial evidence demonstrates that the Chronic Care Model can improve chronic care and, in some cases, reduce healthcare costs [8,9,13]. However, more research is needed to substantiate the relative effectiveness of the components of this model.

One element of the Chronic Care Model that has not been studied extensively, but which nevertheless may offer a realistic opportunity to improve chronic care, is the use of clinical information systems. These include reminder systems that help primary care teams comply with practice guidelines, and feedback to physicians showing how they are performing with regard to quality of care indicators. Practice recommendations (which may be based on national or international guidelines) are generally used as a reference for comparison when providing feedback.

Benchmarking, a technique used for quality management in industry since the 1980s, has only recently been introduced into the clinical setting. It consists of measuring the clinical performance of the healthcare delivered by an individual clinician or a clinic over a specified period (termed the audit), comparing it with the performance of a peer group or a group of similar clinics (benchmarking), and transmitting this comparison back to the clinician or clinic (benchmarked feedback) (Figure 1). Benchmarking therefore encompasses an intellectual, emotional and/or competitive stimulus for change. It also offers an opportunity to break through the isolation that many primary care physicians encounter, as they are not routinely able to compare their performance with that of their peers.

**Figure 1 F1:**
[figure not shown]
**Example of benchmarking and feedback process**.

It would appear to be intuitively logical that if healthcare professionals were given feedback that their clinical practice, and therefore their patient outcomes, was inconsistent with that of their peers or accepted guidelines, they would modify their attitude and practice. However, there are few published reports of randomised studies investigating this approach in T2DM in primary care, and the effectiveness of feedback and benchmarking has not been definitively proven in a randomised, controlled setting. OPTIMISE (OPtimal Type 2 dIabetes Management Including benchmarking and Standard trEatment) was designed as a randomised controlled trial assessing the effect over a 12-month period of physician- and patient-specific feedback with benchmarking on the quality of primary care in T2DM patients from six European countries. The aim of the current paper is to describe the rationale for, and methodology used in the OPTIMISE study, including details of the benchmarking and feedback process.

## Methods

The original protocol developed in Belgium was subsequently adapted for extension to five other European countries: Greece, Luxembourg, Portugal, Spain and the UK. Patient recruitment began in March 2008 in Belgium, and in September 2008 for the other countries.

### Patients

All patients with T2DM (insulin treated or not), aged ≥18 years were eligible for the OPTIMISE study. Exclusion criteria were patients with type 1 diabetes, gestational diabetes, patients who were hospitalised for diabetes regulation or who were members of the Belgian Diabetes Convention (i.e. hospital-based diabetes centres already participating in a quality assurance programme with benchmarked feedback). The definition of diabetes used was a fasting plasma glucose test of ≥126 mg/dL.

### Study design

This randomised controlled trial was performed in accordance with the Declaration of Helsinki and ICH/Good Clinical Practice and applicable regulatory requirements [14]. The study was sponsored by AstraZeneca. Written, informed consent was obtained for all patients before initiation into the study. The OPTIMISE study is registered at ClinicalTrials.gov (NCT00681850).

The aim of the study was to assess the impact of benchmarking on the quality of T2DM care, by determining, as the primary objective, the percentage of patients in the benchmarking group achieving, after 12 months of follow up, pre-set targets of three critical quality indicators (glycated haemoglobin [HbA_1c_], low-density lipoprotein [LDL]-cholesterol and systolic BP [SBP]) versus the control group. The null hypothesis was that the percentage of patients at target after 12 months of follow up in the benchmarking and the control groups would be equal. Secondary objectives included determining the percentage of patients achieving the pre-set targets of the critical quality indicators and glycaemia versus baseline; determining the percentage improvement of the critical quality indicators and glycaemia versus baseline; and to follow up evolution markers of preventative screening (retinopathy, neuropathy, dietary counselling, microalbuminuria, smoking habits, body mass index [BMI], and physical activity).

Centres or sites were selected on the basis of having sufficient patients with diabetes in their practice and with investigators that were motivated to fulfil the administrative procedures linked to the study. Centres or sites were randomised by a central randomisation procedure to either a benchmarking group or a control group. To ensure that country-specific treatment practices were reflected in the study population, the centres or sites involved in the management of diabetes that were recruited, consisted of general practitioner or hospital-based outpatient clinics. Recruitment for the study began initially in Belgium with a randomisation ratio of 1:1. Each centre was expected to recruit 8-12 patients; however, some centres enrolled 15-20 patients. The adapted sample size analysis showed that a power of 79% was achieved for the parameter blood pressure and a significance level of 0.05 was achieved for the parameters HbA_1c _and total cholesterol. As sufficiently high numbers of physicians were recruited in Belgium, this subsequently allowed a 3:1 randomisation ratio of benchmarked to control practices in the other countries, which was deemed more attractive to the participating physicians. All physicians involved in the study continued with the routine monitoring, treatment and counselling of their patients with T2DM. Over the course of the study, physicians in both groups received the results of modifiable outcome indicators (HbA_1c_, fasting glycaemia, total cholesterol, high-density lipoprotein [HDL]-cholesterol, LDL-cholesterol and triglycerides [TG]; determined in a central laboratory). Physicians in the benchmarking group additionally received information on the level of control of the critical quality indicators of their individual patients, anonymously compared with the results of their colleagues from the same country, and compared with target levels (Figure 2). This benchmarked feedback was provided every 4 months, corresponding to three- to four-times yearly control visits, as recommended by international guidelines [15]. The study recruitment and initiation visit was defined as Visit 1 out of the four visits.

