### Target setting for benchmarking

The targets set for the critical quality indicators (HbA_1c_, LDL-cholesterol and SBP) used for benchmarking were based on international guidelines [16-18], and, when deemed necessary, adapted by the study steering committee in order to be consensual to the participating countries (Table 1).

**Table 1 T1:** OPTIMISE Study: Targets set for benchmarking

	SBP (mmHg)	LDL-cholesterol (mg/dL)	**HbA**_**1c**_ (%)
All countries	< 130*	< 100^†^	< 7.0
Belgium		< 80^†^	

*Patients with proteinuria < 125 mmHg

^†^Patients with existing coronary heart disease < 70 mg/dL

For physicians in the benchmarking group, benchmarked feedback was given to each practice for both the pooled patient population at that practice, and at an individual patient level (Figure 3). A bi-modal response was given (good, too high) for each of the critical quality indicators, signifying whether or not the patient/clinic had achieved targets. In Belgium, the National Steering Committee opted for a tri-modal response: HbA_1c _≤7.0% = excellent, 7.1-7.5% = borderline, > 7.5% = too high; SBP < 130 mmHg = excellent, 130-139 mmHg = borderline, ≥140 mmHg = too high; LDL-cholesterol < 80 mg/dL = excellent, 80-99 mg/dL = good, ≥100 mg/dL = too high (< 70 mg/dL = excellent in secondary prevention).

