As some centres included up to 20 patients, sample size calculations were adapted. With 3000 evaluable patients in the benchmarking group (200 clusters of 15 patients) and 1000 patients in the control group (67 clusters of 15 patients), there would be 96%, 93% and 88% power to detect a 74% difference between the proportion of patients on target for SBP for an ICC of 0.05, 0.07 and 0.10, respectively, p = 0.05. With 3000 evaluable patients in the benchmarking group (150 clusters of 20 patients) and 1000 patients in the control group (50 clusters of 20 patients), there would be 93%, 88% and 81% power to detect a 74% difference between the proportion of patients on target for SBP for an ICC of 0.05, 0.07 and 0.10, respectively, p = 0.05.

Descriptive statistics (mean, median, number of observations, standard deviation, standard error, 95% confidence intervals - minimum and maximum) of all primary and other variables will be tabulated. Given the expected clustering of patients for each physician, multilevel mixed modelling will be performed using SAS GLINMIX for categorical variables (target attainment after 12 months in the benchmarking group compared with the control group, and target attainment after 12 months compared with baseline levels) and SAS Prox MIX for continuous variables (mean percentage improvement of HbA_1c_, LDL-cholesterol and SBP after 12 months follow up).

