## Results

Recruitment commenced on 6 March 2008 and finished 31 December 2008. The database lock date was 31 March 2010. A total of 4026 patients, of which 3994 are evaluable, were enrolled from 370 sites across six countries in Europe. In the All Patients group, 55.1% were male. The benchmarking group comprised 2484 patients; the control group comprised 1510 patients (Table 2). Baseline demographics were similar for both groups. Full results will be reported elsewhere.

**Table 2 T2:** OPTIMISE Study: Number of patients participating in each country

Country	Benchmarking	Control	All patients
Belgium	1146	1044	2190
Greece	570	227	797
Luxembourg	136	62	198
Portugal	134	51	185
Spain	257	55	312
UK	241	71	312
Total	2484	1510	3994

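### Allocation ratio differs by country (1:1 in Belgium, 3:1 elsewhere), but the described pooled comparison names only physician clustering and states no country term or stratification

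*Protocol article*

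**What the plan says.** **Allocation (Study design).** Randomisation was by centre: "Centres or sites were randomised by a central randomisation procedure to either a benchmarking group or a control group". The ratio was not constant: "Recruitment for the study began initially in Belgium with a randomisation ratio of 1:1", after which "this subsequently allowed a 3:1 randomisation ratio of benchmarked to control practices in the other countries".

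**Outcome of allocation (Results, Table 2).** "The benchmarking group comprised 2484 patients; the control group comprised 1510 patients". Belgium contributed 1146 benchmarking and 1044 control patients.

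**Analysis (Study design; Statistical considerations).** The null hypothesis is that the two groups have equal percentages at target at 12 months. The sample size treats the trial as one comparison of 3000 with 1000 patients, without strata. On the model the article says: "Given the expected clustering of patients for each physician, multilevel mixed modelling will be performed using SAS GLINMIX for categorical variables". It lists no fixed effects or covariates.

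**Targets (Target setting for benchmarking).** Table 1 gives the same SBP and HbA1c targets for all countries. For LDL-cholesterol it gives <100 mg/dL for all countries and a separate <80 for Belgium, with <70 where there is coronary heart disease. The Belgian feedback grading reads: "LDL-cholesterol < 80 mg/dL = excellent, 80-99 mg/dL = good, ≥100 mg/dL = too high".

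**Bias claim (Discussion).** Among the strengths, the randomised design is said to remove favourable bias from trial participation, from selection of motivated physicians and from general changes in diabetes care during the study.

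**The concern.** When the probability of allocation depends on country, randomisation makes the arms comparable within a country but not across the pooled trial. The control arm is weighted towards Belgium and the benchmarking arm towards the other five countries. This follows from the allocation rule, so a larger sample does not remove it.

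A random physician or site intercept does not remove it either. That term describes the correlation among patients of one physician. Country is a characteristic of the cluster that is associated with arm, and it has to be conditioned on.

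The article itself gives reason to expect country differences. It recruited different types of clinic so that national treatment practice would be represented, and it gives Belgium its own LDL target. If such differences affect attainment, a pooled contrast without country credits part of them to benchmarking, or sets them against it. The bias protection claimed in the Discussion then holds within country but not for that pooled contrast.

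**Working it through.** **1. Inputs and the plan's own totals.** Table 2 adds up: 2484 + 1510 = 3994. Belgium is 1146:1044 = 1.10:1. The other five countries are (2484 − 1146):(1510 − 1044) = 1338:466 = 2.87:1. Both agree with the stated 1:1 and 3:1. The planned SBP effect is 30.6% − 23.2% = 7.4 points.

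**2. Imbalance.** Belgian share of control is 1044/1510 = 69.1%. Belgian share of benchmarking is 1146/2484 = 46.1%. The difference is 23.0 points.

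**3. Bias of a contrast that ignores country, with no true effect.** Let D be non-Belgian minus Belgian attainment. The expected difference, benchmarking minus control, is (0.691 − 0.461) × D = 0.230 × D. It favours benchmarking if D is positive and control if D is negative.

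**4. Type I error.** The article gives no attainment by country, so D is assumed. Further inputs are overall attainment of 30% (assumed), 3994/370 = 10.8 patients per site, and ICC 0.05 to 0.10 (the article's range for blood pressure).

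Design effect = 1 + (10.8 − 1) × ICC = 1.49 at ICC 0.05 and 1.98 at ICC 0.10.

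SE = √[0.30 × 0.70 × (1/2484 + 1/1510) × design effect] = 1.83 points at ICC 0.05 and 2.10 points at ICC 0.10.

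The error is the probability that |Z| > 1.96 when Z has mean 0.230 × D / SE. A simulation under no effect (361 sites of 11 patients, beta-binomial outcomes, cluster-level regression, 2000 runs per setting) was set beside it. In each range the lower value at gaps of 10 points and more is for ICC 0.10.

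| Assumed gap D | Bias | Error, formula | Error, simulation |
|---|---|---|---|
| 5 points | 1.2 points | 8.5-9.7% | about 8% |
| 10 points | 2.3 points | 19-24% | 18-24% |
| 15 points | 3.5 points | 37-47% | 39-49% |
| 20 points | 4.6 points | 59-71% | 62-74% |

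At D = 10 the bias is 2.3/7.4 = 31% of the planned effect. With a Belgium-versus-other term in the same simulation, the mean estimate was within 0.1 point of zero and the error was 4-5%.

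**5. Cost of conditioning on country.** Take information as the sum of n1 × n2/(n1 + n2).
- Pooled: 2484 × 1510/3994 = 939.
- By country: Belgium 546.3, Greece 162.3, Luxembourg 42.6, Portugal 36.9, Spain 45.3, UK 54.8; total 888.
- Ratio: 888/939 = 0.946, a loss of about 5%. The planned 3000:1000 split would have given 3000 × 1000/4000 = 750.

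Power for 23.2% versus 30.6% at the actual allocation (unpooled Z test, same design effect) goes from 98.9% to 98.5% at ICC 0.05, from 97.9% to 97.3% at 0.07, and from 95.8% to 94.8% at 0.10.

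These figures do not rest on the article's printed power for clusters of 10 (91/86/80%). The same method gives 97.3/95.7/92.5% for those inputs; that mismatch is a separate matter.

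**6. LDL target, texts side by side.** The primary objective refers to pre-set targets, and Table 1 holds the only targets given. Read that way, Belgium is scored at <80 and the others at <100. But Table 1 is headed as targets for benchmarking, its <100 row covers all countries, and the Belgian grading calls 80-99 good and only ≥100 too high. Under the first reading the arm with more Belgians (control) is held to the stricter cut-off, which pushes the pooled contrast towards benchmarking. Under a common <100 that component disappears.

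**The case against.** The strongest reply is that the article does not commit to an analysis without country. It names a model class, the software procedures and the reason for a multilevel model. It lists no fixed effects at all, so it neither includes nor excludes country. It is a condensed account, and covariates are commonly left to the full protocol or analysis plan, which are not shown. That stands: a reader might infer that the model has no country term and that country does confound the result, but the text supports only that none is stated. The point is still more than missing detail. The article fixes an allocation rule that depends on country, sizes and describes one pooled comparison, and claims bias protection that this comparison has only if it conditions on country.

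The reply on size also stands. The article has no attainment rates by country, so every gap above is an assumption. For SBP and HbA1c, whose Table 1 targets are common to all countries, even the direction is unknown. A reader might also infer that the LDL result is bound to favour benchmarking, by an amount derived from an assumed LDL distribution. The documents support neither step: the Belgian endpoint cut-off is not settled, they give no LDL mean or SD, and the ICC range is for blood pressure.

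Finally, a reader might add season, because Belgium began recruiting in March 2008 and the others in September 2008. No Belgian closing date, enrolment distribution or seasonal effect is given, so no weight is placed on it.

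**Conclusion.** The concern holds in conditional form. The dependence of arm on country is certain: it is stated, and Table 2 confirms it. If the pooled comparison is run with physician clustering alone, the benchmarking estimate is shifted by 0.23 points for each point of Belgian/non-Belgian difference in attainment. A gap of about 32 points (7.4/0.230) would be needed to produce the whole planned effect, but 5 to 10 points already raises the type I error from 5% to between about 8% and 24%. These error rates assume 30% overall attainment, equal site sizes and an ICC of 0.05 to 0.10. The similar baseline demographics reported in Results do not settle the matter, because country itself is not balanced between the arms.

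**What to change.** - State that the GLIMMIX and MIXED models for the between-arm comparison include country, at minimum Belgium versus other, as a fixed effect or stratum, so that the benchmarking effect is a within-country contrast.
- Report the Belgium and other-country estimates beside the pooled one. Two groups are preferable to six separate estimates, since Portugal, Spain and Luxembourg have only 51, 55 and 62 control patients.
- Reconcile Table 1 with the Belgian grading by stating which LDL cut-off scores the 12-month endpoint in Belgium.
- Qualify the Discussion's claim of bias protection as holding within country.

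The cost is one model term (five parameters if all six countries are used), about 5% of information, and a power loss of about one point or less for the planned effect. If the full protocol or analysis plan already includes country, only the statement in the article, the LDL cut-off and the Discussion sentence need attention.

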**Figure 2 F2:**
[figure not shown]
**Study flow chart**. CRF, case report form; IC, informed consent.

